# The Maudsley model of anorexia nervosa treatment for adolescents and young adults (MANTRa): a study protocol for a multi-center cohort study

**DOI:** 10.1186/s40337-021-00387-8

**Published:** 2021-03-08

**Keywords:** MANTRa, Maudsley model, Anorexia nervosa, Treatment, Psychotherapy, Adolescents, Young adults, Study protocol

## Abstract

**Background:**

The treatment of anorexia nervosa (AN) is often challenging due to medical complications as well as high relapse and mortality rates. Studies about effective treatment options for people with AN are particularly scarce in the adolescent population. This paper is a study protocol for a multi-center cohort study assessing the feasibility, acceptability and efficacy of a new, manualized treatment program, the “Maudsley Model of Anorexia Nervosa Treatment for Adolescents and Young Adults” (MANTRa) compared to psychotherapeutic treatment as usual (TAU).

**Methods/design:**

One hundred patients between 13 and 21 years who meet the inclusion criteria will receive 24 to 34 individual weekly MANTRa therapy sessions or weekly TAU sessions. Primary outcome variables will be BMI and eating disorder psychopathology 12 months after baseline. Further changes in central coherence, cognitive flexibility, emotion recognition, comorbid psychopathology (e.g. depression, obsessive-compulsive and anxiety disorders, non-suicidal self-injury), personality factors and therapeutic alliance will be assessed.

**Discussion:**

This multi-center study will examine the utility of the treatment program MANTRa for adolescents with AN and, therefore enhances the current knowledge about potential treatments for this patient group.

**Trial registration:**

ClinicalTrials.gov Identifier: NCT03535714. Registered: 24/05/2018 (retrospectively registered, still recruiting).

**Supplementary Information:**

The online version contains supplementary material available at 10.1186/s40337-021-00387-8.

## Introduction

Anorexia nervosa (AN) is a severe mental illness characterized by persistent restriction of energy intake, deliberate weight loss and, in further consequence, extreme low body weight [1]. Life-time prevalence among adolescents and young adults range between 0.5 and 1% with females being more affected than males [2, 3].

According to guidelines of the National Institute of Health and Care Excellence (NICE) [4] AN treatment needs to be multidisciplinary including medical care and weight monitoring as well as psychological interventions. Due to medical complications as well as high relapse and mortality rates treatment of AN is often challenging [5, 6]. Only half of all patients receiving AN treatment achieve full recovery after 4 to 10 years [7]. Recently published longitudinal studies showed that after 20 years of suffering from AN, recovery rates are still very low, ranging from 40 to 63% [8, 9].

Studies examining the efficacy of interventions for AN are particularly scarce in the adolescent population. A recent meta-analysis highlighted that there have been only eight published randomized-controlled trials (RCTs) that examined the efficacy of outpatient AN treatment for adolescents, with research dominated by studies comparing different versions of Family Therapy for AN (6 out of 8 studies) [10]. Family Therapy for AN, currently recommended as the only first-line psychological intervention for adolescents [4] has been found to significantly improve eating disorder (ED) psychopathology and weight gain; however, only 41.8% of the participants achieved full recovery at the end of therapy [11] and more than a quarter (26.6%) still suffered from AN after 2 to 4 years [12]. A study from Eisler and colleagues [13] showed significant differences of improvements in AN symptoms in favor of Multi-Family Therapy compared to Single-Family Therapy, possibly due to the fact that relationship patterns become more visible in the multi-family setting [14], but the percentage of patients having a good outcome after 1 year (measured with the Morgan-Russell scale) was limited in both groups ranging from 33 to 45% [13].

Enhanced Cognitive Behavioral Therapy (CBT-E) and Adolescent-Focused Therapy (AFT), the only recommended second-line psychological interventions for adolescents so far [4], have been found to significantly improve ED psychopathology as well as BMI [11, 15], but only 71.4% of patients receiving CBT-E fully completed the treatment while the remaining patients either required additional interventions or dropped-out [15]. Craig and colleagues [16] examined the use of CBT-E in an adolescent sample suffering from AN or atypical AN either as second-line treatment for patients after having received Family Therapy or in cases where Family Therapy was not applicable. They found significant improvements in ED psychopathology, but also a high attrition rate of 38.9% among those who started CBT-E. Altogether, the high rate of non-responders or treatment attrition in the established interventions as well as the lack of research emphasizes the need for the development of new therapeutic approaches in the adolescent population with AN.

MANTRA (Maudsley Model of Anorexia Nervosa Treatment for Adults), a manualized individual treatment program specific for patients with AN was developed by [name] and colleagues [17]. MANTRA’s efficacy has been examined in adults in several studies showing not only significant and stable improvements in ED psychopathology and BMI, but also high treatment acceptability and low drop-out rates [18, 19]. Consequently, MANTRA has been recommended as first-line psychological intervention for adults with AN [4]. This new intervention is centered around a patient’s workbook combining elements of cognitive behavioral therapy (e.g. a diagrammatic case formulation focusing on maintaining factors) and writing tasks, supporting emotion expression and regulation, based on the seminal ideas of James Pennebaker [20]. The therapeutic style of motivational interviewing (MI) is used to increase intrinsic motivation for change and overcome resistance [21].

The theoretical basis of MANTRA is the Cognitive-Interpersonal Maintenance Model of AN [22, 23] which considers predisposing personality traits like obsessive-compulsive and anxious-avoidant traits to be key vulnerability factors enhancing the risk of developing AN and contributing to the maintenance of the illness. Other factors known to maintain the illness and considered in MANTRA are: (1) impairments in the socio-emotional domain like the avoidance of emotions and reduced skills in social processing, (2) an inflexible, perfectionistic and detail-orientated thinking style, (3) pro-anorexia beliefs (positive beliefs about the value or function of the illness or particular symptoms, like ‘AN keeps me safe’ or ‘AN gives me control’) and (4) unfavorable communication styles of parents or close others. In contrast to CBT-E, weight and shape concerns are not considered as the central psychopathology of the disorder, but as symptoms of more profound and troubling problems [24].

Although MANTRA has not been applied to adolescents with AN so far, some of its characteristics might be especially beneficial for adolescents [25]: (1) MANTRA is centered around a patient’s workbook that every patient receives at the beginning of the treatment (for more details see ‘2.4.1 Intervention Group’). The therapist and the patient jointly select themes and exercises from the workbook based on the patient’s needs and symptomatology without a predetermined order. Patients are encouraged to read and perform additional exercises at home. The workbook offers the possibility to deal with therapeutic content outside the weekly therapy sessions, which could further improve treatment outcome [26]. For those not willing to complete homework outside the therapy sessions, exercises can exclusively be covered within the therapy sessions. (2) MANTRA is also conceptualized as a flexible and adaptive treatment program, in which patients are directly involved in the therapeutic process. Patients are encouraged to actively select topics which they want to work on. We assume that the possibility of taking responsibility and making active decisions during the therapeutic process could enhance motivation and self-efficacy which is very important for adolescents, as they strive for autonomy and independence during their normal pubertal development. (3) Additionally, one of the main targets of MANTRA is to enhance the patient’s intrinsic motivation for recovery. The empathic, respectful and accepting therapeutic style of MI aims to overcome resistance and gently guide patients towards recovery. Together, this helps to improve treatment engagement. (4) Another key element of MANTRA are writing tasks. People with AN often experience increased emotionality but at the same time have poorer awareness of emotions and less adaptive emotion regulation strategies than healthy controls [27]. We assume that especially young people with AN could benefit from expressing their thoughts and feelings in writing rather than verbally. Writing tasks may not only allow adolescents to take a broader perspective on their illness, but may also foster cognitive restructuring, reduce emotional avoidance and help generating new solutions [28]. (5) Another characteristic of the MANTRA workbook is the chapter focusing on identity. The ego-syntonic nature of AN and the high value of certain aspects of the illness (e.g. pro-anorexic beliefs) might be particularly relevant during adolescence and emerging adulthood, a developmental stage characterized by identity exploration and self-focus. In MANTRA, role models are used to construct alternative, non-illness-driven beliefs and values and enhance identity exploration and formation [29].

However, it is unclear whether the high acceptability, low dropout rates or improvements in ED psychopathology observed in adult patients receiving MANTRA [18, 19] can be transferred to adolescents with AN. This paper is a study protocol for a multi-center cohort study assessing the feasibility, acceptability and efficacy of an adapted version of the MANTRA treatment program for adolescents and young adults with AN (subsequently named “MANTRa”) compared to psychotherapeutic treatment as usual (TAU). We hypothesize that patients in the MANTRa intervention group will show a BMI increase and a reduction of ED symptoms at 12 months compared to baseline and that MANTRa will be superior to TAU with regard to BMI increase, ED psychopathology and treatment acceptability.

## Materials and methods

### Study design

The trial described in this study protocol paper is a multi-center cohort study, which will evaluate the efficacy of MANTRa (*n* = 50) compared with TAU (*n* = 50) in a sample of adolescent and young adult outpatients with AN. Assessments will be conducted prior to intervention start (baseline, T0), at 6-month (T1), at 12-month (T2) and at 18-month follow-up (T3). Researchers who will not be involved in conducting the medical and psychotherapeutic ED treatment will assess the outcome variables.

Ethical approval was obtained from the Ethics Committee of the Medical University of Vienna (EK 2005/2017). The data collection in this study follows the ethical standards laid down in the 1964 Declaration of Helsinki and its later amendments. The trial was registered at clinicaltrials.gov (Identifier: NCT03535714).

### Study setting, recruitment

This trial will be mainly conducted at three clinical centers in Austria: (1) The Eating Disorder Unit at the Department of Child and Adolescent Psychiatry, Medical University of Vienna, (2) the Department of Child and Adolescent Psychiatry, Medical University of Innsbruck and, (3) the Department of Neurology and Psychiatry for Children and Adolescents of the Clinical Center Klagenfurt. Further patients will be recruited from the “Sowhat Competence Center for Eating Disorders” in Vienna and cooperating child and adolescent psychiatrists in medical practices.

Recruitment for the trial started in April 2018 and is currently on-going. We expect to reach the final sample size in January 2021. Data collection will be completed in July 2022.

### Eligibility criteria

All patients who will receive ED treatment at one of the clinical centers or medical practices will be asked to participate in the study if they meet the inclusion criteria. Patients will be eligible if they:
are aged between 13 and 21are diagnosed with full-syndrome AN, atypical AN or weight restored AN (following inpatient treatment) according to DSM-5are willing to engage in psychotherapy

Patients will be excluded if they:
suffer from life-threatening AN requiring immediate inpatient treatment as defined by the German guidelines for diagnosis and treatment of eating disorders [30]have insufficient cognitive abilities or German language skills to follow the treatment contentsuffer from a severe mental or physical illness that needs priority treatment (for example psychosis, acute suicidality, borderline personality disorder, substance abuse)are pregnant

The eligibility criteria will be checked in appointments (called “Clearing phase”) by the case manager (psychologist, psychiatrist). After checking the eligibility criteria, potential trial participants and their legal representatives will be informed about the study procedures by child and adolescent psychiatrists and/or psychologists not involved in the MANTRa or TAU psychotherapy either in face-to-face meetings or via telephone including the option to ask questions. Written informed consent from one of the legal representatives (if aged below 18) and the patient’s assent will be obtained prior to the inclusion in the study.

### Interventions

MANTRa will be compared to a TAU group covering different non-manualized psychotherapeutic approaches for the treatment of AN. Thus, the TAU group will represent the landscape of currently available psychotherapeutic treatments for adolescent AN in Austria. Therefore, the study does not aim to contrast the MANTRa intervention to another specific therapeutic intervention but to explore its acceptability and efficacy compared with psychotherapeutic interventions that can be regarded as standard care in Austria (e.g. cognitive-behavioral therapy, systemic family therapy, psychodynamic or psychoanalytic therapy or humanistic approaches).

#### Intervention group (MANTRa)

The MANTRa intervention (‘Maudsley Model of Anorexia nervosa treatment for adolescents and young adults’) is an adapted version of the original MANTRA treatment program for adult patients with AN and is designed as an outpatient manualized treatment program consisting of 20 weekly therapy sessions of approx. 50 min. followed by 4 monthly booster sessions. Patients with a more severe illness (one or more comorbidities, BMI below the 3rd sex and age-specific BMI percentile and illness duration longer than 1 year) will receive an extended version consisting of 30 weekly sessions, followed by 4 booster sessions. Whether a patient will receive the longer or shorter version will be decided according to the criteria mentioned above prior to the intervention start.

The original workbook [17] was translated into German and had been adapted to the developmental level of adolescents in terms of language, design and content by our research team. A tabular description of the differences between MANTRA for adults compared to MANTRa for adolescents according to the TIDieR framework [31] is provided as supplementary material. For example, explanations for technical terms were inserted and a form of address customary for young people was used. In terms of content, we created three case vignettes representing typical adolescents suffering from AN, which are introduced in the first chapter and occur in every chapter explaining certain exercises. The case vignettes enable the patient to identify with adolescents who experienced similar events and who could serve as role models on the way to recovery. In chapter four, we changed nutritional recommendations according to suggestions of our dieticians who are experienced in the field of adolescent’s EDs (e.g. portion sizes are illustrated using the hand proportions and fists, not focusing on calories) and added information and exercises for managing binge eating and purging behavior. Dietological exercises of chapter four, such as the creation of a meal plan and nutritional recommendations are carried out by dieticians (see section ‘2.4.5. Relevant concomitant care permitted during trial’). BMI tables were replaced by BMI-percentile graphs. In chapter seven, which addresses emotions, we added the distress tolerance exercises from the Dialectic-Behavioral Therapy for Adolescents [32], because adolescents suffering from AN often engage in non-suicidal self-injury behaviors or experience emotion regulation problems [33]. Thus, adolescents need effective tools to help dealing with and expressing overwhelming emotions, as well as understanding the emotion regulation function of AN [34]. We also added a new chapter about social media and mobile applications to the workbook which was based on materials provided by South London and Maudsley NHS Foundation Trust [35], because social media platforms provide the opportunity and risk to communicate and exchange illness related as well as health-related thoughts known to be frequently used by adolescents [36]. Discussions about helpful and unhelpful aspects of social media platforms can be important for adolescents. Furthermore, we also adapted the design and layout of the workbook to make it more appealing for adolescents by creating each chapter in a different color and adding icons for better visual recognition of recurrent content (e.g. a letter icon for writing tasks or a question mark for reflection exercises). An overview of the chapters of the adolescent version of the workbook can be found in Table 1.

**Table 1 Tab1:** Chapters of the MANTRa patient’s workbook

Chapter	Title	Content / Aim
1	Introduction to MANTRa	Introduction to MANTRa, description of setting and treatment efficacy, case vignettes
2	The journey begins	Enhancing motivation for change, pro and cons of the illness
3	Nobody is an island – support from others	Social environment, families, support through others
4	Physical health and nutrition	Physical health, healthy nutrition, meal plans, dietary
5	My Anorexia	Case formulation, causing and maintaining factors of the illness, vicious flower
6	Treatment goals	Developing treatment goals, SMART goals
7	Emotions and social relationships	Emotion recognition and regulation skills, social relationships and roles, the inner critic voice, self-compassion
8	Thinking styles	Perfectionism, detail-orientation, rigidity and inflexibility
9	Social media	Social media as maintaining factor of the illness
10	Identity	Role models, identity with and without anorexia
11	The flower of life	Relapse prevention, virtuous flower

Similar to the original MANTRA program, close others will be invited to participate in 2 to 3 MANTRa sessions if necessary. The aim of this joint sessions is to discuss conflicts within the family and to develop strategies how close others can support the patient, thus promoting a common understanding of the disease and ways to recovery. Additionally, parents will be included regularly in the medical treatment provided by the case manager and will be invited to participate in the parental skills training “SUCCEAT” (see section ‘2.4.5. Relevant concomitant care permitted during trial’) [37–39].

We recruited clinical psychologists or licensed psychotherapists specialized in cognitive-behavioral therapy from the Department for Child and Adolescent Psychiatry at the Medical University in Vienna or from the Austrian Society for Behavioral Therapy as study therapists. In total, 13 clinical psychologists or psychotherapists agreed to participate. They will conduct the MANTRa intervention with an estimated 1 to 4 patients each in their private practices or in their clinic offices. Beforehand, all therapists attended a 2-days MANTRa training workshop offered by [name] as well as a 1.5-day MI workshop offered by a licensed MI-trainer. Regular team meetings to discuss cases will be organized by the research team and therapists will be encouraged to participate in MANTRa group supervision provided by [name]. The clinician engagement in group supervision will be recorded by the research team. MANTRa therapist will only treat patients in the intervention group.

#### Treatment as usual group (TAU)

Patients in the TAU group will receive outpatient psychotherapy from psychotherapists experienced in EDs, who are licensed as psychotherapists according to the Federal Ministry of Social Affairs, Health, Care and Consumer Protection. Psychotherapeutic approaches of the TAU group cover different, approved methods, like cognitive-behavioral therapy, systemic family therapy, psychodynamic or psychoanalytic therapy or humanistic approaches (e.g. gestalt therapy, logotherapy and existential analysis, etc.). Case managers will suggest a suitable psychotherapist from a pool of AN experienced psychotherapists and will organize an initial treatment appointment in cooperation with the parents. This is the standard procedure for the allocation of patients to psychotherapy in the Austrian health care system, where psychotherapy is mostly provided by external, individual practitioners.

#### Assignment of intervention

Patients undergoing treatment at the Department of Child and Adolescent Psychiatry in Vienna who will not attend any other psychotherapy or psychological treatment or have discontinued their psychotherapy prior to the baseline assessment, will be assigned to the MANTRa intervention group. Patients who will be treated in the other centers or who have already recently started psychotherapy will be assigned to the TAU group. The allocation of patients to the therapists will be based on availability and local proximity in both groups.

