### Outcomes

All outcome variables will be assessed prior to intervention start at baseline (T0) and after 12 months (T2). The primary outcome (ED psychopathology), comorbidities and quality of life will be additionally collected 6 months after baseline (T1) and at 18-month follow-up (T3) (see Fig. 1 for details). Self-report questionnaires will be administered online via ‘LimeSurvey’, while interviews will be conducted face-to-face or via telephone by trained professionals.

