### Statistical analysis

The primary statistical analysis will be based on the intention-to-treat principle, which means that participants will be analyzed in the group to which they were allocated irrespective of their compliance with the assigned treatment. Missing data will be imputed; the specific imputation model will be developed once the final data is available. *T*-tests for paired samples will be carried out for analyzing pre-post differences (T0-T2) in the three primary outcome variables (BMI, EDE, EDI-2). To account for multiple testing (three primary outcome variables) and the inflation of the Type I error rate, we will use Bonferroni correction to adjust the significance level (α = .017). Additionally, a completer analysis will be conducted as a secondary analysis. General linear mixed models will be used to measure effects between groups and over time (T0, T1, T2, T3) with using the treatment type (MANTRa vs. TAU) as between factor and assessment time (T0, T1, T2, T3) as within-factor. The treatment type x time interaction will indicate whether there is a difference in the course between the MANTRa and control group. Additional *t*-tests will be used to explore group differences between intervention (MANTR-a) and control group (TAU).

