### Limitations

A limitation of this paper is the absence of randomization. Instead, patients will be assigned to the group based on predefined criteria, like the presence of a recently started psychotherapy or centre of treatment (for details see 2.4.3 Assignment of intervention). This could lead to an assignment bias, where groups may differ in terms of therapeutic alliance at baseline. However, it would be unethical to disrupt an already existing therapeutic process unless the patient requests it. In order to minimize possible group differences at baseline, we will statistically compare both groups regarding clinical and sociodemographic characteristics (e.g. age, ED severity, educational level) and include them as covariates in the statistical analysis if necessary. Furthermore, group comparability may be limited due to the study settings (e.g., audio recordings and evaluation after the therapy session only in the MANTRa group). Thus, differences between MANTRa and TAU can only be interpreted as observational, not as causal. Nevertheless, the comparison with TAU may serve as a basis for a larger randomized controlled trial.

A sample size of *N* = 50 per group might also be too low to statistically detect small between-group effects; however, the planned sample size represents a reasonable number of patients who can be recruited and involved in the study within the planned time frame. Nevertheless, the planned sample size should be sufficient to explore the feasibility and acceptability of MANTRa compared to TAU as well as to explore the size of effects regarding the treatment success that can be expected. If the results of this study are promising, this information can be used to design a larger randomized-controlled trial.

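### T0 is defined as before treatment for everyone, but part of TAU is already in psychotherapy at T0, so the treatment-by-time comparison lacks a common time origin

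*Protocol article*

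**What the plan says.** Two sections of the protocol article define T0. Study design: "Assessments will be conducted prior to intervention start (baseline, T0), at 6-month (T1), at 12-month (T2) and at 18-month follow-up (T3". Outcomes: "All outcome variables will be assessed prior to intervention start at baseline (T0) and after 12 months (T2". Neither makes an exception for the control group.

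The Assignment of intervention section then fixes who enters each group. MANTRa takes patients of the Vienna department who are in no other psychotherapy or who "have discontinued their psychotherapy prior to the baseline assessment, will be assigned to the MANTRa intervention group". For the control group: "Patients who will be treated in the other centers or who have already recently started psychotherapy will be assigned to the TAU group". The text sets no limit on how long ago the therapy may have begun.

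The section on TAU describes a fresh start, in which the case manager "will organize an initial treatment appointment in cooperation with the parents". The section on additional care, however, rules out two individual psychotherapies at the same time, and Limitations says a therapy under way should not be broken off unless the patient asks. A therapy running at T0 therefore carries on as the TAU treatment.

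For the between-group analysis, Statistical analysis uses a mixed model over T0 to T3: "The treatment type x time interaction will indicate whether there is a difference in the course between the MANTRa and control group". Limitations acknowledges an assignment bias and describes it this way: "groups may differ in terms of therapeutic alliance at baseline". It plans baseline comparisons with covariates where needed, and restricts the group comparison to an observational reading.

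**The concern.** The T0 definition and the assignment rule cannot both hold for TAU patients who are already in therapy. Their T0 value may include some response to the comparator treatment, and that response is lost from their measured change. Their T1, T2 and T3 also fall later in therapy than the same visits do in MANTRa, where every patient is by rule not in another psychotherapy at T0.

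The introduction hypothesises that MANTRa is superior to TAU, and the treatment-by-time interaction is the analysis that addresses this. A reader told that T0 precedes treatment in both groups would misread even a purely descriptive plot of the two courses. The comparison is also meant to inform a later randomised trial, so a distorted effect size would be carried into its planning.

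**Working it through.** **1. The passages side by side**

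| Section | Rule | Consequence for a TAU patient already in therapy |
|---|---|---|
| Study design; Outcomes | T0 precedes intervention start | T0 should be untreated |
| Assignment of intervention | Recently started psychotherapy leads to TAU | Therapy began before T0 |
| Relevant additional care permitted during trial; Limitations | No second individual therapy; existing therapy not interrupted | The running therapy is the TAU treatment |
| Statistical analysis | Time coded T0, T1, T2, T3 in both groups | T0 is treated as a common origin |

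The remark about therapeutic alliance at baseline fits this reading, since an alliance can exist at T0 only if therapy is already running.

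**2. Do the planned covariates help?** Limitations gives age, eating disorder severity and educational level as examples. Severity at T0 is already partly treated in the affected patients, so conditioning on it does not recover their untreated starting point. A centre term does not help either. Vienna-department patients without current therapy all go to MANTRa, so that department has no newly starting TAU patients to compare with.

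**3. The plan's own figures**

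- Paired t-test, dz = 0.5, two-sided 5%: n = 34 gives power 0.808, as stated. Dropout: 34 / (1 − 0.25) = 45.3, so 46; the planned 50 covers this.
- Interaction, N = 100, two time points, correlation 0.5 (my assumption; not stated): 80% power is reached at f = 0.1415, which agrees with the stated 0.14.
- The same sensitivity as a difference in mean change: the noncentrality is f² × N × m / (1 − ρ) = 0.1415² × 100 × 2 / 0.5 = 8.0. Setting d² × 50 / 2 = 8.0 gives d ≈ 0.57 SD of change.

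None of these figures depends on the T0 problem. The 0.57 SD serves as the yardstick below.

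**4. Possible size, under assumptions the documents do not supply**

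Let p be the share of TAU already in therapy at T0 and g the fraction of their change that came before T0. Take a 12-month change of 0.5 SD in both groups (the article's dz, borrowed for TAU) and no true group difference. Assume that each gain before T0 is subtracted in full from later change. Then

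spurious difference = p × g × 0.5 SD of change.

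| p | g | Spurious difference (SD) | Two-sided rejection at 5%, 50 per group |
|---|---|---|---|
| 0.10 | 0.10 | 0.005 | 5.0% |
| 0.25 | 0.25 | 0.03 | 5.3% |
| 0.50 | 0.50 | 0.125 | 9.5% |
| 0.75 | 0.50 | 0.19 | 15.3% |

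These rates count rejections in both directions. With no bias, a two-sided 5% test falsely favours MANTRa 2.5% of the time.

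**5. What a restricted analysis would leave.** If TAU is limited to patients starting at or after T0, 50 × (1 − p) remain: 45 at p = 0.10, about 37 at p = 0.25 and about 12 at p = 0.75. Against 50 MANTRa patients, setting d² × n₁n₂/(n₁ + n₂) to the noncentrality for 80% power gives detectable differences of about 0.58, 0.61 and 0.92 SD.

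**The case against.** The strongest reply is that this matters little. The only tests that are both powered and Bonferroni-adjusted are the paired T0–T2 comparisons within MANTRa, and they do not use TAU data. The article discloses that a recently started therapy decides assignment, says this may bias the comparison, plans covariates and disclaims causal interpretation. All of this stands and lowers the severity. It does not remove the contradiction, because the article nowhere says that T0 follows treatment start for some TAU patients.

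Three stronger readings are tempting, and the documents support none of them.

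- **That the comparison is biased in favour of MANTRa.** Lost early gain would favour MANTRa. But placing patients who stay in therapy in TAU and those who discontinued in MANTRa may act the other way, as may the longer time in therapy that these TAU patients have by T2. The net direction is open.
- **That false-positive findings are greatly inflated.** With a 75% share and 0.5 SD gained before T0, the spurious difference is 0.375 SD and the rejection rate about 46%. That requires recently started patients to have gained the whole planned 12-month effect before T0. The 75% share has no support either, since TAU also draws on several sources outside the Vienna department and is described as beginning with an arranged first appointment. If improvement is roughly steady over time, the bias is near zero.
- **That the trial's primary result is compromised.** The within-MANTRa tests are untouched.

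It may also be said that therapy start dates belong in the full protocol. That is fair as far as their absence from the article goes. The point here is the conflict between rules that the article does state.

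**Conclusion.** The contradiction is real and rests on the text alone. For an unstated part of TAU, T0 is not a pre-treatment assessment, and the treatment-by-time interaction compares courses that start at different points in therapy. The planned covariates cannot repair this.

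The consequence is confined to the between-group comparison, which the article already treats as observational. Its size and direction cannot be derived from the documents. Under the assumptions in the working it ranges from negligible (0.005 SD) to about a third of the detectable difference (0.19 / 0.57 = 0.33). It should be corrected before analysis, but it does not invalidate the study.

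**What to change.** - State in Study design and Outcomes that T0 may follow the start of therapy for some TAU patients, so that both agree with Assignment of intervention.
- Record for each TAU patient the start date of the index psychotherapy and the number of sessions before T0.
- Keep the all-TAU comparison as planned. Pre-specify two sensitivity analyses: one restricted to TAU patients whose therapy began at or after T0, and one accounting for weeks in therapy at T0.
- Name the unequal time origin in Limitations, alongside therapeutic alliance.

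The cost is two data items per TAU patient and some wording. Whether the items can still be obtained for patients already enrolled is not stated and needs checking; the article expects data collection to end in July 2022.

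The restricted analysis has fewer TAU patients. It also confounds treatment fully with centre, because every MANTRa patient would come from the Vienna department and every remaining TAU patient from elsewhere. For that reason it should be a sensitivity analysis and not replace the main contrast.
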